### 6.4 Outcomes and variables

Determination of fasting blood glucose levels, glycated hemoglobin (HbA1c), total cholesterol, triglycerides, and high density lipoprotein cholesterol (HDL-C), low-density lipoprotein cholesterol (LDL-C) and liver function enzymes-AST (aspartate aminotransferase), ALT (alanine aminotransferase), alkaline phosphatase (ALP), and  $\gamma$ -glutamyltranspeptidase (GGT), adipokines (adiponectin, leptin, visfatin, resistin, and

plasminogen activator inhibitor-1 (PAI-1)), pancreatic hormones (Glucagon, Insulin and C-peptide) and gut hormones (ghrelin, glucose-dependent insulintropic polypeptide (GIP) and glucagon-like peptide 1 (GLP-1)). To assess kidney function, serum creatinine, urea and urine albumin will be measured. Albumin concentrations will be measured in fasting urine samples. Microalbuminuria and macroalbuminuria will be diagnosed if the albumin excretion is between 30 and 299 µg/mg and was  $\geq 300$  mg/g of creatinine, respectively. We will assess the impact of filarial infection on gut leakage during obesity by screening the plasma for the microbial translocation markers LPS-binding protein (LBP), endogenous endotoxin-core antibodies (EndoCAb), systemic LPS levels and intestinal fatty acid-binding protein (iFABP). Acute-phase proteins alpha-2-macroglobulin ( $\alpha$ -2M), C-reactive protein (CRP), haptoglobin, and serum amyloid A protein (SAA).

- Insulin resistance calculated based on HOMA-IR
- Total and differential leucocyte counts as well as absolute and relative quantification of naïve, effector and central memory CD4+ and CD8+ T cells, regulatory T cells, NK cells, subset of monocytes, dendritic cells and B cells in whole blood via flow cytometry in a subset of n=30 in each group
- Frequencies of intracellular cytokine-producing cells of in vitro whole blood cell cultures in response to PMA/ionomycin, anti-CD3/anti-CD28, Pam3Cys, LPS, or palmitic acid determined by flow cytometry in a subset of n=30 in each group
- Pro- and anti-inflammatory cytokines and chemokines in plasma, whole blood culture supernatants analysed by multiplex cytokine assays
- Total humoral immune responses in serum IgG1, IgG2, IgG3, IgG4, IgA, and IgE and antibody titres against parasite antigens quantified by ELISA
- Microfilariae burden in *Mansonella*, *Loa loa* and *O. volvulus* patients.
- Height, weight, waist circumference, body fat, blood pressure and electrocardiogram using standard techniques. Calculation of BMI
- Analysis of the above mentioned parameters over a period of 3 years, in 6-month intervals

#### **6.5 Analysis whether termination of *Mansonella* and Onchocerciasis infection via 6-week Doxycycline (200mg per day) treatment will change the metabolic and immunological profiles (analysis according to the descriptions above) 12 and 18 months post treatment. Overall timeline of the study**

Patient recruitment & anti-filarial therapy

Follow-up 1 – 12 months after treatment onset

Follow-up 2 – 18 months after treatment onset

## **7 SELECTION AND INCLUSION OF VOLUNTEERS**

### **7.1 Inclusion criteria**

Patients eligible for the study must comply with all of the following:

- Participants will be male and female between 18-60 years old
- BMI equal to or above 25 or below 25
- Body weight > 40kg
- Last intake of ivermectin at least 4 months ago
- Last intake of anti-filarial antibiotic treatment more than 12 months ago
- Resident in the endemic study area for at least 5 years

- *O. volvulus* patients, microfilariae skin snip positive and/or PCR positive for *O. volvulus*
- *M. perstans* or *Loa loa* patients positive for microfilariae and/or PCR
- Endemic controls, judged by absence of microfilariae, palpable onchocercoma, PCR negative for *M. perstans* and *O. volvulus*. Individuals should be free of other helminth infections and possess normal eosinophil frequencies (0.5-4%).
- Good general health without any clinical condition requiring long-term medication
- Normal white blood cell counts ( $3.5-11.3 \times 10^3/\mu\text{l}$ )
- Willingness to participate in the study as evidenced by signing the Informed Consent Form or parental signature in the ICF for subjects less than 21 years

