### 6.3 Group allocation

Volunteers of both sexes (stratified according to age, gender and socio-economic status) with a BMI above  $\geq 30$  (obese) and  $< 25$  (lean), will be assigned to the following groups according to the clinical assessment (Fig. 1):

- 200 obese and 200 lean individuals with onchocerciasis (presence of microfilariae in the skin, *O. volvulus* PCR positive). All onchocerciasis patients will be treated with 200mg doxycycline daily for 6 weeks. They will also receive single dose of 400 mg albendazole every three months with a total of 4 treatments. *M. perstans*, *O. volvulus* as well as *Loa loa* co-infected individuals will be included and treated with doxycycline and albendazole, in case that not sufficient individuals with *O. volvulus* infection alone are identified.
- 200 obese and 200 lean individuals with *M. perstans* (presence of microfilariae in the blood, PCR positive). All *M. perstans* infected obese and lean patients will be randomly selected for anti-filarial therapy with 200mg of doxycycline daily for 6 weeks. They will also receive single dose of 400 mg albendazole every three months with a total of 4 treatments. *M. perstans* and *O. volvulus* as well as *Loa loa* co-infected individuals will be included and treated with doxycycline and albendazole, in case that not sufficient individuals with *M. perstans* infection alone are identified.
- 200 obese and 200 lean *Loa loa* infected and 200 obese and 200 lean healthy endemic individuals without onchocerciasis, *Mansonella perstans* infection with normal eosinophil counts and IgE levels. All endemic individuals will receive single dose of 400 mg albendazole every three months with a total of 4 treatments.

[figure not shown]

Fig. 1: Distribution of study participants

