## 10 STATISTICAL CONSIDERATIONS

### 10.1 Sample size justification and statistical analysis

This is a partially randomized controlled open label pilot trial to gain first experience on the impact of infections with the filarial nematodes *O. volvulus* and *M. perstans* on the metabolic profile and the systemic immune response in lean and obese patients. As there is limited data that exists to inform on study design, we will use 400 persons per group (*O. volvulus* infected, *M. perstans* infected, and endemic non-helminth-infected persons) with half of the participants of each group having a BMI of  $\geq 30$  and the other half of below 25. Thus, cases (those with active worm infections) and controls (worm infection free) will be included at a case: control ratio of 1:1:1. All *M. perstans* infected patients and all *O. volvulus* infected persons will further be treated in an interventional pilot study to test the changes in the metabolic profile and the systemic immune responses following treatment with doxycycline.

Our primary endpoint will be quantitative changes in insulin resistance (HOMA-IR). The logarithmic transformed HOMA-IR values will be compared between the three obese subgroups with a two-step test procedure. In the first step a one factorial analysis of variance will be used to test the hypotheses of equal mean log(HOMA-IR) values in the three groups at a level of 5%. In case that this hypothesis can be rejected the mean log(HOMA-IR) values will be checked for equality for each pair of groups with a two-sided t-test at a level of 5% for each test. This test procedure maintains a multiple level of 5%. From literature data (33) we expect the logarithm of the HOMA-IR to be normally distributed with a standard deviation of 0.83. With the planned sample size of 200 cases per group the intended test procedure then has a power of 80% to detect a deviation of 0.3 in the mean log(HOMA-IR) values between two of these groups. This is equivalent to reduction of 25% of the HOMA-IR in comparison between these two groups.

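### The upper BMI stratum is ≥25 in the synopsis and 7.1 but ≥30 in 6.3 and 10.1, so the population of the primary test cannot be determined

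*Protocol*

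**What the plan says.** Five places in the current protocol text define the strata. The lower stratum is below 25 in all of them; the upper one differs.

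- **Synopsis, Participants:** BMI ≥25 or <25.
- **Synopsis, Study groups:** BMI ≥25 with n=200, and BMI <25 with n=200, in each of the four groups.
- **7.1 Inclusion criteria:** "BMI equal to or above 25 or below 25".
- **6.3 Group allocation:** ≥30, labelled obese, and <25, labelled lean, with 200 of each per group.
- **10.1 Sample size:** 400 per group, "with half of the participants of each group having a BMI of" at least 30 and the other half below 25.

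Section 10.1 then fixes the primary analysis: "Our primary endpoint will be quantitative changes in insulin resistance (HOMA-IR"). The log-transformed "values will be compared between the three obese subgroups with a two-step test procedure": an ANOVA at 5%, then each pair "with a two-sided t-test at a level of 5% for each test". The inputs are 200 per subgroup, log(HOMA-IR) "normally distributed with a standard deviation of 0.83", and a difference of 0.3, for which 80% power is stated.

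**The concern.** The primary test is restricted to one BMI stratum, so the cut-off decides who is in it. The only numerical definition of obese in the protocol is the one in 6.3, BMI ≥30. The sections that govern eligibility and the recruitment targets use ≥25.

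A team that recruits to 7.1 and the synopsis will fill the 200 places with a mixture of overweight and obese people. An analyst who follows 10.1 will find that some of them belong to neither half of the group. The protocol does not say whether they enter the primary test or count towards the 200. If this is settled once HOMA-IR results are available, in an open-label study, the primary population becomes open to choice on the data.

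**Working it through.** **Side-by-side reading for a person with BMI 27**

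| Section | Eligible or allocated? | Counts towards the upper 200? |
|---|---|---|
| Synopsis, Participants and Study groups | yes | yes |
| 7.1 | yes | not stated there |
| 6.3 | no stratum | no |
| 10.1 | no stratum | no |

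No other section reconciles the two cut-offs or defines obese as ≥25.

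**The plan's own power figure.** Inputs from 10.1: n=200 per group, σ=0.83, δ=0.3, two-sided 5%. The placement of the third group is not given. I put it midway, which is the least favourable case for the ANOVA.

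- ANOVA: λ = nδ²/(2σ²) = 200 × 0.09 / (2 × 0.6889) = 13.06. With 2 and 597 df the critical F is 3.01, and power is 90.8%. With the third group at one extreme it is 96.9%.
- Pairwise t-test: noncentrality δ/(σ√(2/n)) = 0.3/0.083 = 3.61, and power is 95.0%.
- Both steps together, by simulation: about 90–91%.

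The stated 80% is therefore below what its own inputs give. That is a separate matter; it is noted here only because the illustrations below start from 91% and 95%.

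**Route A: overweight people stay in the test, n=200.** Let w be the share of the stratum with BMI 25 to <30, and r the effect there relative to the effect at ≥30. Both are assumptions; the protocol gives neither. The mean difference is 0.3 × [1 − w(1 − r)], with the SD held at 0.83.

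| w | r | Mean difference | ANOVA | Pairwise |
|---|---|---|---|---|
| any | 1 | 0.300 | 91% | 95% |
| 0.5 | 0.5 | 0.225 | 68% | 77% |
| 0.7 | 0.5 | 0.195 | 54% | 65% |

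For the second row, λ = 200 × 0.0506 / 1.3778 = 7.35 and the t noncentrality is 0.225/0.083 = 2.71.

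**Route B: overweight people are dropped, δ=0.3.** The subgroup size becomes 200 × (1 − w).

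| w | n per subgroup | λ | ANOVA | Pairwise |
|---|---|---|---|---|
| 0.25 | 150 | 9.80 | 80% | 88% |
| 0.50 | 100 | 6.53 | 62% | 72% |
| 0.75 | 50 | 3.27 | 34% | 43% |

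The contradiction stands on the text alone. The tables show only that the choice of route can matter.

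**The case against.** The strongest defence is that either cut-off is a legitimate design, that the mismatch probably reflects an incomplete update, and that a statistical analysis plan could name the analysis population. The first part is right: this is an inconsistency, not a poor choice of cut-off. The rest does not remove the problem. All the sections are current text in the same protocol version, and an analysis plan cannot make eligibility and allocation rules agree with each other.

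Several stronger readings are tempting but not supported:

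- A reader might infer that the stated power is valid only for BMI ≥30. Section 10.1 takes the SD of 0.83 from the literature without tying it to a BMI band, and gives 0.3 as a detectable difference, not as an effect expected in people with BMI ≥30. All that can be said is that the calculation is written for a stratum that the enrolment text does not match.
- A reader might take the lower power figures as the cost of the contradiction. They depend on an assumed share and an assumed effect ratio; with the same effect in both bands the loss under route A is nil.
- A reader might count the 7.1 line, which excludes no BMI, as a second defect. Beside the synopsis strata it works as a stratification line. People are left without a stratum only when it is set against 6.3 and 10.1, which is the same contradiction.

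**Conclusion.** The point holds as an internal contradiction that affects the primary analysis. Three places (two synopsis rows and 7.1) use ≥25, two (6.3 and 10.1) use ≥30, and the primary test is confined to the stratum in dispute. Its population cannot be determined from the protocol as written, so the passages need to be reconciled.

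The size of the consequence is unknown. Under the labelled assumptions (SD 0.83, third group midway), ANOVA power ranges from no loss at 91% to 68% when half the stratum is overweight with half the effect, and to 62% when that half is excluded instead. These figures show what is at risk; they are not predictions, and the finding does not rest on them.

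**What to change.** Use one cut-off in the synopsis, 6.3, 7.1 and 10.1, and define the population of the primary test in 10.1 to match. Which cut-off is for the sponsor to decide.

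- **If ≥25 is kept:** describe the stratum as overweight or obese wherever obese now names it (4.1, 4.3, 6.1, 6.3, 9.3 and 10.1), state that the sample-size calculation applies to that stratum, and report the BMI ≥30 subset as a sensitivity analysis.
- **If ≥30 is kept:** change 7.1 and both synopsis rows. State how anyone already enrolled with BMI 25 to <30 is handled and whether they count towards the 200.

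Adjustment for continuous BMI is not part of this fix. The Background (4.2) cites lower BMI with helminth infection in one human study and reduced body weight in some animal work. BMI could therefore lie on the causal path, and adjusting for it could remove part of the effect under study.

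Cost: keeping ≥25 needs wording changes and one extra analysis on BMI data already collected. Keeping ≥30 may cost more. The footnote in 7.2 refers to 2000 people already screened, and if any were enrolled with BMI 25 to <30, replacements may be needed to reach 200 per subgroup.

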| Study groups           | 
Group 1: Mansonella patients
 
 
Positive for Mansonella perstans
 
Microfilariae (Mf) positive and/or M. perstans PCR positive
 
BMI <math>\geq 25</math> (n =200)
 
BMI <math>< 25</math> (n =200)
 
 
Group 2: Onchocerciasis patients
 
 
Positive for Onchocerca volvulus
 
Microfilariae (Mf) positive and/or O. volvulus PCR positive
 
BMI <math>\geq 25</math> (n =200)
 
BMI <math>< 25</math> (n =200)
 
 
Group 3: Endemic normal
 
 
Mf negative in skin and blood
 
O. volvulus and M. perstans PCR negative
 
Negative for other filarial and helminth infections
 
Normal range of eosinophils and IgE levels
 
BMI <math>\geq 25</math> (n =200)
 
BMI <math>< 25</math> (n =200)
 
 
Group 4: Loiasis patients
 
 
Positive for Loa loa
 
Microfilariae (Mf) positive and/or Loa loa PCR positive
 
BMI <math>\geq 25</math> (n =200)
 
BMI <math>< 25</math> (n =200)
 
 |

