Consistent with these human studies, a series of mechanistic studies in diet-induced obese mice revealed that helminth infections/helminth derived product administration induced protective type 2 immune responses, expanded eosinophils, ILC2s and AAM (5-7). This correlated with reduced glucose intolerance, hepatic steatosis and in some cases decrement in body weight and adipose tissue mass (8). Identified protective immune responses included the mitigation of adipose inflammation partly through IL-10 and suppressed hepatic lipogenesis (9), the triggering of the IL-33/ILC2 axis (10), induction of eosinophil and AAM expenditure in adipose tissue (6) and eventually stimulation of adipose tissue browning as type 2 immune responses are a promoter of browning, which increases energy expenditure (13, 27).

Besides the mentioned cross-sectional reports on humans and mechanistic studies on animal models, there is no longitudinal follow-up study that investigated the causal link between helminth infections, immunomodulation and metabolic responses. In light of the enormous global diabetes burden and the beneficial effect of helminth-induced immunomodulation on diabetes, it is important to elucidate the effect of helminth infections and their eradication on diabetes. Therefore, we aim to decipher the influence of immunomodulation by infections with the filarial nematodes *Mansonella perstans*, *Loa loa* and *Onchocerca volvulus* on glycemic and metabolic parameters in Southwest Cameroon, an endemic area for filarial infections.

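### Only the endemic controls are selected for normal eosinophils and IgE, yet both are listed outcomes, so their contrasts with Group 3 are partly set by the entry rule

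*Protocol*

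**What the plan says.** The control group carries a requirement that the infected groups do not.

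- **Controls.** Section 7.1: "Individuals should be free of other helminth infections and possess normal eosinophil frequencies (0.5-4" (per cent). The synopsis, under Group 3, asks for "Normal range of eosinophils and IgE levels". Section 6.3 describes the endemic individuals as free of *Mansonella* "infection with normal eosinophil counts and IgE levels". Section 7.1 does not repeat the IgE condition.
- **Infected groups.** Section 7.1 admits *M. perstans* and *Loa loa* "patients positive for microfilariae and/or PCR", and *O. volvulus* "patients, microfilariae skin snip positive and/or PCR positive for" that species. Neither entry has an eosinophil or IgE limit.
- **All groups.** Section 7.1 requires "Normal white blood cell counts". This bounds the total count, not the eosinophil share of it.
- **Outcomes.** Section 6.4 lists total and differential leucocyte counts and "Total humoral immune responses in serum IgG1, IgG2, IgG3, IgG4, IgA, and IgE". Section 4.1 says the responses are compared with obese and lean endemic controls. Section 5.1 makes the association of infection with the systemic immune response part of the primary objective.
- **Rationale.** Section 4.2 gives eosinophilia and raised IgE as features of the type 2 response to helminths. It reports that in diet-induced obese mice helminth infection or helminth products "induced protective type 2 immune responses, expanded eosinophils, ILC2s and AAM", and that this went with less glucose intolerance.

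The protocol gives no reason for the control-only rule and does not discuss what it does to the comparison.

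**The concern.** A group selected to lie within limits on a variable is not a fair comparator for that variable. If any truly uninfected residents exceed the limits, Group 3 understates the eosinophil and IgE levels of uninfected people. Infected groups would then look higher even if infection did nothing. Adjustment for age, sex or BMI does not undo this, and people who were never enrolled cannot be recovered in the analysis.

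A second, conditional effect concerns the primary endpoint. The protocol's rationale is that type 2 responses, including expanded eosinophils, improve glucose handling. If that also holds for uninfected people, choosing controls with low eosinophils would raise their mean log(HOMA-IR) and push the comparison towards the expected result.

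**Working it through.** **The plan's own figure.** The protocol gives no number for the effect of this rule. Its only figure for the infected-versus-control comparison is in section 10.1: 80% power for a difference of 0.3 in log(HOMA-IR), SD 0.83, 200 per group. A pairwise two-sided t-test at 5% on those inputs gives 95.1%, and the two-step procedure about 90% to 94% by simulation. That mismatch is a separate matter. Only the 0.3, the 0.83 and the 200 are used below. The 0.3 is consistent with the stated 25% reduction, since exp(-0.3) = 0.741.

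**Step 1: effect on the selected marker.** Assume a marker that is standard normal in infected people and in parasite-negative residents alike (no infection effect), with controls kept only below the upper limit. With pass share p, c = Φ⁻¹(p):

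- control mean m = -φ(c)/p
- control variance v = 1 - c·φ(c)/p - (φ(c)/p)²
- z of the contrast with 200 per group = |m| / √((1 + v)/200)

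For p = 0.9: c = 1.282, φ(c) = 0.1755, m = -0.1755/0.9 = -0.19, v = 0.71, z = 0.195/√(1.71/200) = 2.1.

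| Assumed pass share | Control mean (SD units) | Control variance | z |
|---|---|---|---|
| 90% | -0.19 | 0.71 | 2.1 |
| 70% | -0.50 | 0.49 | 5.7 |
| 50% | -0.80 | 0.36 | 9.7 |
| 30% | -1.16 | 0.26 | 14.6 |

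The pass shares are assumptions. Section 6.4 can be read as placing differential counts in the subset of 30 per group. In that case each z is multiplied by √(30/200) = 0.387, giving about 0.8, 2.2, 3.7 and 5.6. The shift in the mean is unchanged.

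**Step 2: possible effect on log(HOMA-IR).** Assume eosinophil percentage in parasite-negative residents is log-normal with median M and log-SD s, and correlates r with log(HOMA-IR). With a = ln(0.5/M)/s and b = ln(4/M)/s:

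- pass share = Φ(b) - Φ(a)
- mean of those passing, z̄ = (φ(a) - φ(b)) / (Φ(b) - Φ(a))
- shift in the control mean = r × 0.83 × z̄

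| M, s (assumed) | Pass share | z̄ | Shift, r = 0 | Shift, r = -0.1 | Shift, r = -0.3 |
|---|---|---|---|---|---|
| 2%, 0.6 | 87% | -0.21 | 0 | 0.017 | 0.051 |
| 3%, 0.6 | 68% | -0.51 | 0 | 0.043 | 0.128 |
| 4%, 0.6 | 50% | -0.80 | 0 | 0.066 | 0.198 |
| 6%, 0.6 | 25% | -1.27 | 0 | 0.106 | 0.317 |
| 8%, 0.6 | 12% | -1.65 | 0 | 0.137 | 0.411 |

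The standard error of a pairwise difference is 0.83 × √(2/200) = 0.083, and the planned difference is 0.3. Depending on inputs the protocol does not contain, the shift runs from nothing, through 0.2 standard errors (0.017), to about 5 (0.411).

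**Step 3: what is untouched.** Section 10.1 compares three obese groups in pairs. The *M. perstans* versus *O. volvulus* pair does not involve controls. Within-person change after treatment in the infected groups does not depend on how controls were chosen.

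**The case against.** The strongest defence is that the rule cleans the control group. Section 4.2 treats eosinophilia and raised IgE as the mark of helminth infection. Detection is limited: two skin snips, small finger-prick volumes and stool examination (sections 8.2 and 9.2). The control PCR criterion names *M. perstans* and *O. volvulus* but not *Loa loa*. Allergy, autoimmune disease, acute infection and other chronic infections are excluded in all groups (section 7.2). Many of those who fail the limit could therefore carry undetected infection, and removing them sharpens the infected-versus-uninfected contrast. This stands as a reason to keep the rule. It also means the calculations above, which treat everyone removed as a true control, overstate the distortion where that is so.

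It does not rescue the eosinophil and IgE contrasts. Some uninfected people can exceed 4% for other reasons. The footnote in section 7.2 reports low neutrophils regardless of infection status among 2000 people screened, and fewer neutrophils can raise the eosinophil percentage at an unchanged absolute count.

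A reader might infer that the primary HOMA-IR result is biased in favour of the hypothesis. The documents do not support that as a statement of fact. The eosinophil evidence in section 4.2 comes from obese mice and partly concerns adipose tissue. IgE is named as a type 2 marker, not as a mediator. Nothing is said about blood eosinophils and HOMA-IR in uninfected people.

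It may also be said that section 10.1 specifies no eosinophil or IgE test against controls, and that reporting detail belongs in a statistical analysis plan. But the entry rule, the outcome list and the comparison with controls are all fixed in this protocol, and together they produce the problem.

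**Conclusion.** The concern holds for eosinophils and total IgE. Differences from Group 3 on these two markers are partly produced by selection and should not be interpreted as effects of infection. This needs only that some truly uninfected residents fail the limits. The size depends on the unknown pass share: 0.19 to 1.16 SD for shares of 90% down to 30%.

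For log(HOMA-IR) the concern is conditional. The shift is zero if eosinophils and type 2 status are unrelated to insulin resistance in uninfected people. It is about 0.02 to 0.05 with an assumed median of 2% and r from -0.1 to -0.3, and up to about 0.4 with a median of 8% and r = -0.3. The documents do not allow a choice within that range, so this is a limitation to state, not a demonstrated bias.

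A reader might also conclude that Group 3 must be redefined by parasitology alone. That does not follow. It would trade one source of error for another, because the rule may be removing undetected infections. If controls are already enrolled, the comparison would also mix two control definitions.

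**What to change.** 1. State in section 6.4 that eosinophil counts and total IgE are not outcomes in any comparison with Group 3. Report them only among the infected groups and as within-person change after treatment in those groups.
2. State that Group 3 was selected for normal eosinophils and IgE, and give this as a limitation wherever the HOMA-IR contrast with Group 3 is interpreted, with the direction it could take if the protocol's rationale is right.

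No change to section 7.1 eligibility is asked for, and no extra tests or participants are needed. The cost is the loss of two marker comparisons with controls. The wording can go into the next protocol revision, which section 9.9 already makes subject to ethics permission.
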